**Total = walking + moderate physical activity + vigorous physical activity**

**CLASSIFICATION CRITERIA:**

Moderate Physical Activity:

1. 3 or more days of vigorous physical activity at least 20 minutes per day.

2. 5 or more days of moderate physical activity and/or walking at least 30 minutes per day.

3. 5 or more days of any combination of walking, moderate or vigorous physical activity achieving at least a total of 600 METs*.

Vigorous Physical Activity:

1. Vigorous Physical Activity at least 3 days per week achieving a total of at least 1500 METs*.

2. 7 days of any combination of walking, moderate physical activity and/or vigorous physical activity, achieving a total of at least 3000 METs*.

** Unit of measurement of the test.*

RESULT: ACTIVITY LEVEL (tick as appropriate)

HIGH LEVEL

MODERATE LEVEL

LOW OR INACTIVE LEVEL

**d. EQ-5D Questionnaire**

Please check the statement in each section that best describes your health status today.

**Mobility**

I have no problems walking

I have some problems walking

I have to stay in bed

**Personal Care**

I have no problems with personal care

I have some problems to wash and dress myself

I am uncapable of washing and dressing myself

**Everyday Activities** (e.g., working, studying, chores, family activities)

I have no problem performing my everyday activities

I have some problems performing my everyday activities

I am uncapable of performing my everyday activities

**Pain/Discomfort**

I have no pain nor discomfort

I have moderate pain or discomfort

I have a lot of pain or discomfort

**Anxiety/Depression**

I am not anxious or depressed

I am moderately anxious or depressed

I am very anxious or depressed

To help people describe how good or bad their state of health is, we have drawn a thermometer-like scale on which the best imaginable state of health is marked 100 and the worst imaginable state of health is marked 0.

Please draw a line from the box that says "your health today" to the point on the scale that, in your opinion, indicates how good or bad your health is today.

[figure not shown]

**Your health status today**

Best possible health

Worst possible health

**C. Pulse Wave Velocity (PWV)**

Carotid-femoral PWV is determined by ultrasound using an iE33 (Philips Medical Systems, USA), with an S 113 transducer (7-10 MHz). First, the time between the R wave of the ECG and the onset of the systolic Doppler wave in the right common carotid artery is measured. Subsequently, the time between the ECG R-wave and the foot of the systolic Doppler wave in the radial and femoral artery is measured. For each measurement, 6 cardiac cycles are averaged. The distance between measurement points, marked on the skin, is measured with a specially designed compass avoiding variability attributed to body contour. The PWV is calculated as the distance between the measurement points divided by the carotid-femoral or carotid-radial time difference (transit time of the pulse wave between the two points), in metres per second. Subjects remain at rest in a quiet, temperature-controlled room 10 minutes prior to measurements, which will be performed in the morning and according to published procedures 6. All measurements will be performed by the same scout.

## Variables

1. Principal Variable

Since the main objective is adherence to a physical activity program, the main variable of the study is the METS-minute/week measure. Obtained from the IPAQ questionnaire.

1. Secondary variables

1. Clinical data: age, sex, STEMI, NSTEMI, unstable angina, stable angina, number of vessels, number of stents, complete revascularisation, active smoking, former smoker, hypertension, dyslipidaemia, diabetes mellitus, left ventricular ejection fraction, beta-blockers, ACE inhibitors/ARBs, statins, dual antiplatelet therapy.

2. Socio-occupational data: active worker, days until return to work after discharge.

3. Physical examination: systolic blood pressure, diastolic blood pressure, heart rate, body mass index (BMI), waist circumference, hip circumference.

4. Exercise test: VO2max, exercise time, maximal heart rate, maximal blood pressure, recovery time, ST decline, angor.

5. Pulse wave velocity.

6. Analytical data: glucose, creatinine, total cholesterol, LDL cholesterol, HDL cholesterol, triglycerides, CRPus, HbA1c.

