## Secondary Objectives

Very the improvement of the following parameters, after the intervention:

- Demonstrate an increase in oxygen consumption (VO2max).

- Demonstrate increased exertion time.

- Demonstrate an increase in workload.

- Decrease the presence of symptoms.

- Obtain improvement in lipid profile

- Decrease in ultrasensitive C Reactive Protein (CRPus)EQ

- Demonstrate increased adherence to the Mediterranean diet.

- Demonstrate improved results in psychological state.

- Demonstrate increased willingness to quit smoking and smoking cessation.

- Demonstrate a decrease in the sedentary lifestyle indicator.

- Improved measurement of carotid-femoral pulse wave velocity.

- To evaluate the cost per patient/month in the control cases of conventional rehabilitation and extended tele-rehabilitation intervention.

- To evaluate the time to return to work.

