## Secondary Objectives

Verify the improvement of the following parameters after the intervention:

A. Stress test:

● Demonstrate increase in VO2max.

● Demonstrate increase in exertion time.

● Demonstrate increase in workload.

● Decrease the presence of symptoms.

B. Analytical:

● Obtain improvement in lipid profile.

● Decrease in CRPus.

C. Lifestyle:

● Demonstrate increased adherence to Mediterranean diet.

● Demonstrate improved outcomes in psychological state.

● Demonstrate increased willingness to quit smoking and smoking cessation.

● Demonstrate a decrease in the sedentary lifestyle indicator.

● Demonstrate an earlier return to work.

D. Arterial stiffness

Improving carotid-femoral pulse wave velocity measurement

E. Socio-economic variables

To evaluate the cost per patient/month in the control cases of conventional rehabilitation and extended tele-rehabilitation intervention.

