## Methodology of statistical analysis

The characteristics of the patients in the two study groups will be described (applying the appropriate estimators according to the type of variables, such as means and confidence intervals, medians and interquartile ranges or proportions) and possible differences between the groups will be assessed using appropriate statistical tests of differences of means, distributions of ranks or proportions. The comparison of the primary variable and the secondary variables of the study in both groups at baseline, at four months and 10 months after the start of rehabilitation will be carried out using Pearson χ2 test for qualitative variables (Fisher exact test for dichotomous variable) or Student t-test for independent samples for quantitative variables (Mann-Whitney U test when parametric assumptions couldn’t be assumed). The treatment effects within groups (at four months or ten months) will be assessed using McNemar-Bowker test of symmetry for qualitative variables (McNemar test for dichotomous variable) or Student t-test for paired samples for quantitative variables (Wilcoxon signed-rank test when parametric assumptions couldn’t be assumed). The relationship between quantitative variables will be assessed by Pearson’s correlation coefficient (Spearman’s rank correlation coefficient when parametric assumptions couldn’t be assumed). Multiple linear regression models will be used to assess the significance and magnitude of the intervention effect controlling for possible differences in patient characteristics between groups. In general, backward-forward models will be used, initially constructing the complete models and excluding non-significant variables one at a time (p for variable removal: 0.10) but trying to include the previously removed variables after each exclusion (p for incorporation: 0.05. The analysis will be performed on an intention-to-treat basis. For the economic evaluation, the unit cost will be obtained by quantifying the consumption of resources and applying the official cost rates of the Valencian Health Agency or, if these are not available, they will be estimated by assessing the time and cost of the resources involved. Two-sided exact p-values will be calculated whenever possible and p-values ≤ 0.05 were considered statistically significant. Data will be analysed using IBM SPSS Statistics 22 and R 4.0.2 for Microsoft Windows.

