## Economic evaluation: cost-effectiveness analysis

The study includes a cost-effectiveness analysis to assess the costs and impact on health-related quality of life of the telerehabilitation intervention compared to in-hospital rehabilitation and the control group. The cost analysis will be carried out from the funder's perspective, including direct health care costs (pathology-related emergency visits, hospitalisations for the same cause, diagnostic and therapeutic tests such as revascularisations...) during follow-up. It will also include the costs derived from the intervention, which in the case of conventional rehabilitation, the programd schedule includes 16 rehabilitation visits, 8 rehabilitation sessions (with a physiotherapist, a nurse and a nursing assistant per session) and 8 educational talks. In the telerehabilitation group, the schedule includes 4 rehabilitation visits, 3 sessions (with a physiotherapist and a nurse) and 4 educational sessions. Unscheduled visits and sessions during the follow-up will also be included. The unit costs will be obtained from the Generalitat Valenciana catalogue.

Additionally, an analysis will be performed from a social perspective, including also indirect health care costs due to lost productivity of the patient (number of sick leaves and time to return to work after the event). Indirect costs will be reported by the patient in the follow-up data collection logbook. Effectiveness will be assessed by the physical activity performed by the patient, reported by the patient at the end of the follow-up, measured in METs-minutes/week.

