**SOCIO-OCCUPATIONAL SITUATION**

| Active worker until the event (Y/N) |  |
| --- | --- |

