**SOCIO-OCCUPATIONAL SITUATION**

| Active worker (Y/N) |  |
| --- | --- |
| Time to return to work after discharge (días) |  |

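### Return to work is a censored time, but the protocol assigns it a t-test or Mann-Whitney test and gives no rule for patients not yet back

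*Protocol*

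**What the plan says.** The Summary's Secondary Objectives include "To evaluate the time to return to work"; the fuller list in section 4.2 says "Demonstrate an earlier return to work". Section 7.3 (Variables) lists, among the secondary variables, "active worker, days until return to work after discharge". In Annex 1 the month-4 and month-10 forms collect a yes/no field for active worker and one number, "Time to return to work after discharge (días". The randomisation visit records "Active worker until the event (Y/N".

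Section 9.3 (Methodology of statistical analysis) covers "The comparison of the primary variable and the secondary variables of the study in both groups at baseline, at four months and 10 months" and names the "Student t-test for independent samples for quantitative variables", with Mann-Whitney as the fallback when parametric assumptions fail, Fisher's exact test for dichotomous variables, and multiple linear regression for adjusted effects. It states an intention-to-treat basis. No survival method is named there or in the Summary.

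Section 9.4 (Economic evaluation) uses "number of sick leaves and time to return to work after the event" for lost productivity in the societal analysis.

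**The concern.** Days to return exist only for patients who have returned. A prior worker still off work at the visit, or lost before it, has a lower bound and not a value. The named tests offer two ready ways to handle that patient, and both are poor.

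- Leave the field blank. The comparison is then among returners only. That group is selected after randomisation, by an outcome the intervention is meant to change, which conflicts with the stated intention-to-treat basis.
- Enter the elapsed follow-up. A censored time is then averaged as though the patient had gone back that day.

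At stake is whether the comparison of days can answer the objective of an earlier return. A programme that brings more people back, some of them late, can look slower among returners. The same field feeds the societal cost analysis, where the handling of non-returners is also left open.

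**Working it through.** **The plan's own figure.** The protocol gives no expected return rate, no number of prior workers and no power for this outcome, so there is nothing to reproduce. All return times below are assumptions; they show a range.

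**Inputs.** Follow-up of 10 months (section 6.4, Methods), taken as c = 304 days, and 120 days for the month-4 comparison. Exponential return with rate λ = ln 2 / median. Conventional and telerehabilitation medians keep a ratio of 1.5.

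**Formulas.**
- Proportion back by c: p = 1 − exp(−λc)
- Mean among returners: 1/λ − c·exp(−λc)/p
- Restricted mean over all patients: p/λ

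**One case in full, medians 240 and 160 days.**
- Conventional: 1/λ = 346.2, p = 0.584; returners-only mean 346.2 − 304 × 0.416/0.584 = 130.0; restricted mean 0.584 × 346.2 = 202.3.
- Telerehabilitation: 1/λ = 230.8, p = 0.732; returners-only mean 230.8 − 304 × 0.268/0.732 = 119.6; restricted mean 0.732 × 230.8 = 169.0.
- Differences: 10.5 days among returners and 33.4 days restricted mean; 10.5/33.4 = 31%.

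**Range at 304 days.**

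| Medians (conventional / tele) | Back by day 304 | Returners-only difference | Restricted-mean difference | Kept |
|---|---|---|---|---|
| 240 / 160 | 58% / 73% | 10.5 | 33.4 | 31% |
| 90 / 60 | 90% / 97% | 20.3 | 33.4 | 61% |
| 60 / 40 | 97% / 99% | 21.1 | 26.6 | 79% |
| 45 / 30 | 99% / 99.9% | 19.1 | 21.1 | 90% |

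**Month 4.** With c = 120 in the same formulas, medians 240/160 give 1.7 against 7.8 days (22% kept), and medians 45/30 give 7.2 against 14.1 days (51% kept). Even quick return leaves a marked loss at the earlier comparison.

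**Reversal.** Suppose half of each arm returns at day 90, and telerehabilitation brings a further 30% back at day 240.
- Returners-only means: (0.5 × 90 + 0.3 × 240)/0.8 = 146 against 90 days, so telerehabilitation looks 56 days slower.
- Restricted means: 45 + 72 + 0.2 × 304 = 178 against 45 + 0.5 × 304 = 197 days, so it is 19 days better.

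**Power.** In 2000 simulated trials per setting, with assumed mean return times of 150 v 250 days, 10 to 27 workers per arm and follow-up to day 300, power was 6–10% for Mann-Whitney on returners only, 13–33% for Mann-Whitney with non-returners ranked last, and 18–38% for log-rank.

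**Time origin.** Section 7.3 and the month-4 and month-10 forms count from discharge; section 9.4 counts from the event. The two differ by at least the hospital stay.

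**The case against.** Four points on the other side have force.

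1. A reader might infer that the plan drops patients who have not returned. No section says so. Section 9.3 states intention to treat, and a Mann-Whitney test with non-returners ranked last would be acceptable under a common follow-up. A statistical analysis plan might specify that. This stands as a limit on the claim. But the protocol has already named the tests, Mann-Whitney enters only when parametric assumptions fail, and the one deferral to a statistical analysis plan (section 12.2, on withdrawals) concerns withdrawn patients.

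2. Work status is itself a listed secondary variable, collected at months 4 and 10, and falls under Fisher's exact test. In the reversal example, 80% against 50% back would appear beside the misleading means. So it goes too far to infer that the better arm would simply be reported as worse. Status at two visits still does not measure how early people return, and does not correct the comparison of days.

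3. Enrolled patients are described as low risk (section 13.2) and must have an ejection fraction of at least 50%. Return may be quick, in which case the month-10 distortion is modest. That is why the lower rows of the table belong beside the first.

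4. A reader might infer that indirect costs will be understated. Section 9.4 prescribes no test for costs and does not exclude non-returners; their days off work could be counted. What stands is that it does not say so.

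**Conclusion.** The point holds as a mismatch between the variable and the assigned methods, together with a missing rule for patients not back at work. It does not establish that non-returners will be excluded, or that costs will be too low.

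If the analysis falls back on returners only, the month-10 difference keeps between about 31% and 90% of the restricted-mean difference across the assumed medians, and between about 22% and 51% at month 4 for the slowest and fastest settings. Reversal is possible but needs extra late returners in the better arm. These figures rest on exponential return, a 1.5 ratio of medians and no other losses, none of which the protocol supplies.

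This is one secondary outcome among an unstated number of prior workers. Even log-rank had low power in the setting simulated, and the primary result is unaffected. The change is worth making because it is cheap and the named tests do not match the stated objective.

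**What to change.** In section 9.3, and in the matching Summary text, exempt return to work from the general rule for quantitative variables:

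- Restrict the analysis to patients coded as active workers until the event at the randomisation visit.
- Analyse time to return as time to event, censored at last contact or month 10, with Kaplan-Meier curves, a log-rank test and the difference in restricted mean days to month 10.
- Report the proportion back at work at months 4 and 10 beside it, in the same patients.
- State one time origin and use it in sections 7.3 and 9.4 and in Annex 1.
- In section 9.4, state that patients not back at work contribute days off work up to last contact or month 10.

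Cost: a wording change and slightly more analysis. Work status, days to return and visit dates are already on the forms. Annex 1 has no field for the discharge or event date, so the chosen origin date must be taken from the medical history, which section 5 already lists as a source.

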# Adverse Reactions

All adverse reactions or suspected adverse reactions should be recorded on the Data Collection Notebook sheets in the Adverse Reactions section.

For all adverse reactions, the investigator should seek and obtain sufficient information to determine the outcome of the adverse reaction and to assess whether it meets the criteria for classification as a serious adverse reaction (see section on "Serious Adverse Reactions") which should be reported immediately to the competent authorities. The investigator should obtain sufficient information to determine the causality of the adverse reaction.

## Notification Period

Serious adverse events will be reported by the principal investigator within 1 day to the study monitor or Nabelia staff by telephone or FAX. Incidents and consequences of the serious adverse event should be reported in writing within 4 days. The adverse reaction form should be completed for fatal cases and, whenever possible, all deaths occurring within 30 days after the end of the study should be reported.

According to current legislation, the study sponsor must report serious adverse events to the Spanish Agency for Medicines and Health Products (AEM) and to the Ethics Committee of the corresponding hospital.

The maximum notification period shall be 15 calendar days from the time of knowledge of the suspected adverse reaction. When the suspected serious and unexpected adverse reaction has resulted in the death of the subject, or has endangered his life, the sponsor shall inform the AEMPS within a maximum of 7 calendar days from the moment the sponsor becomes aware of the case. This information should be completed, if possible, within the following 8 days. For adverse reactions occurring in clinical trials conducted in Spain, the number assigned by the EMA to the corresponding protocol must be explicitly mentioned.

The sponsor shall notify the CEIC and the competent bodies of the Autonomous Community individually and within a maximum of 15 days of all suspected adverse reactions which are both serious and unexpected associated with the investigational product. This maximum period shall be 7 days in the case of suspected life-threatening or life-threatening adverse reactions.

The safety report shall either be a part of the corresponding annual and final report or be prepared independently. In either case, the annual and final reports shall contain in tabular form all adverse events detected in the trial up to the time of their preparation.

For all aspects related to adverse events, the guidelines established by the AEMPS shall be followed.

## Adverse Reaction Definition

An adverse reaction is any undesirable event that occurs to a patient who has started the rehabilitation program.

Examples of adverse reactions include the following:

- Clinically significant symptoms and signs.

- Changes in physical examination findings.

## Serious Adverse Reactions

A serious adverse reaction is any unwanted medical event that:

- Causes death;

- Is life-threatening (immediate risk of death);

- results in hospitalisation or prolonged hospitalisation;

- Causes persistent or significant disability or incapacity;

- Is considered medically important by the investigator or sponsor.

## Register and Report of Adverse Events and Serious Adverse Events.

Adverse events shall be recorded in the appropriate section of the data collection logbook (DCL).

# Statistical Analysis

## Sample size calculation

## The sample size is determined by the number of patients eligible for inclusion in the study who are seen in each hospital during the inclusion period. Thirty patients will be included in each of the following groups: control group, conventional rehabilitation group and telerehabilitation group. For the calculation of the power of the study, a 12% possible loss to follow-up has been estimated. Thus, accepting an alpha risk of 0.05 in a bilateral test with 27 subjects in the control group and 27 patients in the intervention group, the power of the hypothesis test is 95% to detect as statistically significant the difference between the mean of 5000 in the first group and the mean of 4000 in the second group after rehabilitation. Based on the potential impact of the telerehabilitation intervention on compliance with the physical activity recommendation at 10 months follow-up, and considering METs-minutes/week as the unit of measurement, it has been estimated that patients in the intervention group will perform 5000 METs-minutes/week while in the conventional rehabilitation group they will perform 4000 METs-minutes/week. It is estimated that physical activity in the non-rehabilitation group will be significantly lower.

## Description of the randomisation process

After agreeing to participate in the study, subjects will be assigned to follow the conventional rehabilitation or telerehabilitation program, according to a block randomisation, estimated using a conventional statistical program.

Subject eligibility will be established prior to allocation to rehabilitation type and inclusion will be sequential. If a subject withdraws from the study his/her randomisation number will not be re-used and re-entry into the study will not be allowed.

